| PT-INR       | prothrombin time-international normalized ratio |
| RAM          | retinal arterial microaneurysm                  |
| RPE          | retinal pigment epithelium                      |
| SAE          | serious adverse event                           |
| SMH          | submacular hemorrhage                           |
| tPA          | tissue plasminogen activator                    |
| VEGF         | vascular endothelial growth factor              |

## 1. Summary of the Study Plan

### 1.1. Overview of the Clinical Trial Protocol

#### ◆ Protocol Title

A Multicenter, Single-Arm, Pre-Post Comparison, Phase II, Investigator-Initiated Clinical Trial to Evaluate the Efficacy and Safety of Sub-Retinal Administration of a Tissue Plasminogen Activator (Monteplase) Preparation for Sub-Macular Hemorrhage

#### ◆ Short Title

A Study of the Safety and Efficacy of a Tissue Plasminogen Activator Preparation for Sub-Macular Hemorrhage

#### ◆ Regulatory Agency Identifier

jRCT2071250003

#### ◆ Rationale

Tissue plasminogen activator (tPA) is an enzyme involved in the fibrinolytic system; it forms a complex with fibrin and activates plasminogen to plasmin, thereby degrading fibrin and exerting thrombolytic activity. In patients with sub-macular hemorrhage (SMH), sub-retinal administration of tPA has been reported (off-label use) to reduce fibrin-mediated photoreceptor and retinal pigment epithelium injury, thereby mitigating visual loss. This Phase II, investigator-initiated trial is planned to assess the efficacy and safety of sub-retinal tPA (Monteplase, recombinant) administered in conjunction with vitrectomy, with the aim of expanding the indication of tPA or developing an ophthalmic formulation for the severe ophthalmic condition of SMH.

#### ◆ Objectives and Endpoints

| Objective                                                                                                                                    | Endpoints                                                                |
|----------------------------------------------------------------------------------------------------------------------------------------------|--------------------------------------------------------------------------|
| Primary                                                                                                                                      |                                                                          |
| To evaluate the efficacy of sub-retinal Monteplase (recombinant) on central macular hemorrhage in patients with SMH secondary to AMD or RAM. | Change in central foveal thickness(CFT) from baseline at Week 1.         |
| Secondary (Efficacy)                                                                                                                         |                                                                          |
| Evaluation of the efficacy of sub-retinal Monteplase (recombinant) in patients with                                                          | <Efficacy Evaluation Items>
1) Change in CFT from baseline at Week 4. |

|                                                                                                        |                                                                                                                                                                                                                                                                                                                                                                   |
|--------------------------------------------------------------------------------------------------------|-------------------------------------------------------------------------------------------------------------------------------------------------------------------------------------------------------------------------------------------------------------------------------------------------------------------------------------------------------------------|
| SMH secondary to AMD or RAM, using ophthalmic examination findings as indices.                         | 2) Presence or absence of a foveal hemorrhage measuring $\geq 1$ disc diameter at Week 4.
3) BCVA (logMAR equivalent) at Week 4.
4) Change in BCVA (logMAR equivalent) from baseline at Week 4.
5) Change in CFT from baseline at Week 12.
6) BCVA (logMAR equivalent) at Week 12.
7) Change in BCVA (logMAR equivalent) from baseline at Week 12. |
| Secondary (safety)                                                                                     |                                                                                                                                                                                                                                                                                                                                                                   |
| To evaluate the safety of subretinal administration of montepilase (recombinant) in patients with SMH. | Adverse events                                                                                                                                                                                                                                                                                                                                                    |

◆ Overview of the Overall Design

Intervention model: Single-arm

Control: Baseline control

Active comparator: None

Allocation method: None

Blinding: None

Target population type: Adult patients

Target population diagnosis: Submacular hemorrhage due to AMD or RAM

Target population age range: Minimum 18 years; no maximum

Distribution of study sites: Multicenter collaborative

Trial phase: Phase II

Committee: None

Duration per subject: 12-week observation period after enrollment

Planned sample size: 20 subjects

◆ Brief Summary of Trial Intervention and Observation

After obtaining written informed consent from the patient, those who satisfy all inclusion criteria and do not meet any exclusion criteria will be enrolled. Enrolled subjects will undergo pars plana vitrectomy, followed by subretinal administration of the investigational product diluted to 80,000 IU/mL, 0.1 mL (8,000 IU). Subsequently, a gas tamponade or silicone-oil exchange will be performed (Day 1). The primary endpoint will be assessed at 1 week post-

procedure (Day 8, Week 1), and secondary efficacy endpoints will be observed at 1 month (Day 29, Week 4) and 3 months (Day 85, Week 12) post-procedure. Adverse events will be collected throughout the observation period for safety evaluation.

#### ◆ Trial Implementation Period

1 August 2025 – 31 October 2027 (Enrollment period: through 31 March 2027; Observation period: through 30 June 2027)

#### 1.2. Study Flow Diagram

[figure not shown]

#### 1.3. Schedule of Activities (SoA)

| Activity                                     | Consent         | Screening             | Enrollment | Treatment period                 |                |                |                |                | Observation period |                 |                 |                 |                 | Discontinuation    |
|----------------------------------------------|-----------------|-----------------------------------|------------|----------------------------------|----------------|----------------|----------------|----------------|--------------------|-----------------|-----------------|-----------------|-----------------|--------------------------------|
| Visit                                        |                 |                                   |            | Visit 1                          | Visit 2        | Visit 3        | Visit 4        | Visit 5        | Visit 6            | Visit 7         | Visit 8         | Visit 9         | Visit 10        |                                |
| Week                                         |                 | Within 7 days before registration |            | 0                                |                |                |                | 1              | 2                  | 3               | 4               | 8               | 12              |                                |
| Day                                          |                 |                                   |            | 1                                | 2              | 3              | 4              | 8              | 15                 | 22              | 29              | 57              | 85              |                                |
| Visit window (Day)                           |                 |                                   |            | Within 7 days after registration | —              | —              | —              | -1~+3          | $\pm 3$            | $\pm 3$         | $\pm 3$         | $\pm 7$         | $\pm 7$         | +7                             |
| Intervention                                 |                 |                                   |            | ○                                |                |                |                |                |                    |                 |                 |                 |                 |                                |
| Trial site                                   | Telemedicine    | Telemedicine / In-person visit    | Enrollment | Hospitalization                  |                |                |                |                | Telemedicine       | Telemedicine    | In-person visit | Telemedicine    | In-person visit | Telemedicine / In-person visit |
| Partner site                     | In-person visit | In-person visit                   |            |                                  |                |                |                |                | In-person visit    | In-person visit |                 | In-person visit |                 | In-person visit                |
| Informed consent                             | ○               |                                   |            |                                  |                |                |                |                |                    |                 |                 |                 |                 |                                |
| Registration                                 |                 |                                   | ○          |                                  |                |                |                |                |                    |                 |                 |                 |                 |                                |
| Medical and ophthalmic history               |                 | ○                                 |            |                                  |                |                |                |                |                    |                 |                 |                 |                 |                                |
| Height · Weight                              |                 | ○                                 |            |                                  |                |                |                |                |                    |                 |                 |                 |                 |                                |
| Vital signs                                  |                 | ○                                 |            | ○                    | ○              | ○              | ○              | ○              |                    |                 | ○               |                 | ○               | ○                              |
| Fundus camera · OCT examination              |                 | ○                     |            |                                  |                |                |                |                | ○                  | ○               | ○               | ○               | ○               | ○                              |
| Visual acuity examination                    |                 | ○                     |            |                                  |                |                |                |                | ○                  | ○               | ○               | ○               | ○               | ○                              |
| Intraocular pressure · Slit-lamp examination |                 | ○                     |            |                                  | ○  | ○  | ○  | ○  | ○                  | ○               | ○               | ○               | ○               | ○                              |
| Fundus examination                           |                 | ○                     |            |                                  | ○  | ○  | ○  | ○              | ○                  | ○               | ○               | ○               | ○               | ○                              |
| Blood test                                   |                 | ○                     |            |                                  |                | ○              |                |                |                    |                 |                 |                 |                 | ○                  |
| Urine test                                   |                 | ○                     |            |                                  |                | ○              |                |                |                    |                 |                 |                 |                 | ○                  |
| Pregnancy test                               |                 | ○                                 |            |                                  |                |                |                |                |                    |                 |                 |                 |                 |                                |
| Chest X-ray                                  |                 | ○                     |            |                                  |                |                |                |                |                    |                 |                 |                 |                 |                                |
| Electrocardiogram                            |                 | ○                     |            |                                  |                |                |                |                |                    |                 |                 |                 |                 |                                |
| Concomitant medications / therapies          |                 |                                   |            |                                  |                |                |                |                |                    |                 |                 |                 |                 |                                |
| Adverse events                               |                 |                                   |            |                                  |                |                |                |                |                    |                 |                 |                 |                 |                                |

\*1 If a partner medical institution is not available, the clinical trial site shall be visited.

\*2 Either the partner medical institution or the trial site may be used. When multiple test results are available within the period, the data closest to the enrollment date shall be used.

\*3 If data are available within 7 days after enrollment, they may be used even before consent acquisition.

\*4 Measured before and after dosing.

\*5 Performed only on the treated eye.

\*6 May be performed at the trial site or at the partner site. If performed at the partner site, the trial site will provide remote medical care.

\*7 Performed only if discontinuation occurs before Visit 3.

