## <Estimand for the Primary Objective>

Primary clinical question: In patients with SMH due to AMD or RAM, regardless of the use of VEGF-inhibitor therapy or the use of tPA formulations for other diseases, what is the change in central foveal hemorrhage volume at the 1-week time point after subretinal administration of montepilase (recombinant)?

|                                    |                                                                                                                                                                                                                 |
|------------------------------------|-----------------------------------------------------------------------------------------------------------------------------------------------------------------------------------------------------------------|
| i. Treatment condition of interest | Subretinal administration of montepilase (recombinant)                                                                                                                                                          |
| ii. Population                     | Patients with SMH defined by the inclusion criteria (severe sub-macular hemorrhage in which spontaneous resolution is not expected, the bleed involves the fovea, and marked visual-acuity loss is anticipated) |
| iii. Endpoint                      | Change from baseline to week 1 in CFT measured by optical coherence tomography (OCT)                                                                                                                            |
| iv. Other intercurrent events      | See Table 3-1                                                                                                                                                                                                   |
| v. Population-level summary        | Mean change from baseline to week 1 in CFT                                                                                                                                                                      |

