Rationale for the estimand: In SMH, the thickness of the central foveal hemorrhage is known to affect visual prognosis. CFT measured by OCT represents the combined thickness of the retina and the hemorrhage at the fovea, thereby reflecting the volume of the central foveal hemorrhage and also allowing assessment of hemorrhagic pigment-epithelial detachment, which is related to visual outcome. Consequently, CFT measured by OCT was selected as the variable constituting the primary estimand. Even when considering the potential impact of VEGF-inhibitor use after montepilase administration or the use of tPA formulations for other diseases, an early reduction in OCT-measured CFT is considered important for regulatory authorities and for individuals involved in determining the therapeutic strategy for the target patient population. Moreover, the persistence of SMH adversely affects visual prognosis; therefore, early displacement of the SMH is important. Accordingly, the 1-week time point, at

which OCT measurement of CFT can be performed without interference from gas tamponade introduced during vitrectomy, was designated as the assessment time point for the primary estimand.

<Estimand for the Secondary Objective (1)>

Clinical question of interest: In patients with SMH due to AMD or RAM, regardless of the use of VEGF-inhibitor therapy or the use of tPA formulations for other diseases, what is the change in ophthalmic examination findings at the 4-week time point after subretinal administration of monteplase (recombinant)?

|                                    |                                                                                                                                                                                                                                                                                                                     |
|------------------------------------|---------------------------------------------------------------------------------------------------------------------------------------------------------------------------------------------------------------------------------------------------------------------------------------------------------------------|

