## 8. Trial Assessments and Procedures

- ✓ The timing of trial evaluations is described in Section 1.3 Schedule. The procedures described in this section and the Schedule in Section 1.3 must be adhered to.
- ✓ Data obtained as part of routine clinical care and collected prior to obtaining informed consent for this trial may be used as screening or baseline data provided that they meet the criteria specified in the protocol and were performed within the time windows defined in the Schedule of Section 1.3.
- ✓ If a serious problem affecting trial continuation arises (e.g., a pandemic), alternative methods for subject visits, assessments, and monitoring may be implemented in accordance with regulatory authority and ethics committee requirements.
- ✓ For safety reasons or technical issues related to assessments, re-evaluation or off-schedule evaluations may be performed.

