## 8.2. Efficacy Assessment Procedures

### 8.2.1. Optical Coherence Tomography (OCT) (both eyes)

Using OCT under mydriasis, capture fundus images and measure CFT ( $\mu\text{m}$ ). Enter the measurement results and the instrument used in the case report form. When measurements are performed at the same medical institution, the same device shall be used throughout the clinical trial period, in principle.

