### 9.3. Analyses Supporting the Primary Objective

#### 9.3.1. Primary Endpoint

The primary endpoint shall be the change from baseline in CFT at week 1.

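### The Schedule of Activities marks no OCT at Visit 5 (Week 1), although the primary endpoint is OCT-measured foveal thickness at Week 1

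*Protocol*

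**What the plan says.** **The endpoint.** Section 1.1 gives the primary endpoint as "Change in central foveal thickness(CFT) from baseline at Week 1", and its summary of the intervention places that assessment at Day 8. Section 9.3.1 repeats it: "The primary endpoint shall be the change from baseline in CFT at week 1". The primary estimand in Section 3 names OCT as the instrument. It explains that Week 1 was chosen as a time at "which OCT measurement of CFT can be performed without interference from gas tamponade introduced during vitrectomy".

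**The schedule.** In Section 1.3, Week 1/Day 8 is Visit 5, during the hospital stay at the trial site. The row "Fundus camera · OCT examination" carries marks at Screening, Visits 6, 7, 8, 9 and 10, and Discontinuation. It has none at Visit 5.

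**The rule that connects them.** Section 8 states: "The procedures described in this section and the Schedule in Section 1.3 must be adhered to". Section 8.2.1 explains how OCT is done and recorded but lists no visits.

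**The concern.** The schedule is the page from which site staff work and to which monitors compare. If it is followed as Section 8 requires, the trial produces no CFT value at the time point on which its only confirmatory test depends. A Week 1 scan that is not taken cannot be recovered later.

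Section 9.2 removes a subject from the FAS only for having no post-dose efficacy data at all, or for a serious GCP violation. A subject with later OCT scans but no Week 1 scan therefore stays in the FAS without an observed primary value. Section 9.1.4 sets no imputation as the general principle, subject to what the SAP specifies. The SAP is not at hand, so how such a subject would finally be treated cannot be stated here.

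**Working it through.** **1. The plan's own figure.** Section 9.9 assumes d = 0.7, two-sided alpha 0.05 and 80% power, and arrives at 19 subjects, then 20 after 5% dropout. For a one-sample t-test, power comes from the noncentral t distribution with n − 1 degrees of freedom and noncentrality d√n.

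- n = 19: noncentrality 0.7 × √19 = 3.05, power 0.823. This is the smallest n that reaches 0.80.
- Dropout: 19 / (1 − 0.05) = 20.

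The figure reproduces. The margin for missing primary values is 20 − 19 = 1 subject.

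**2. Position of the marks.** The table has 15 columns: the activity label, Consent, Screening, Enrollment, Visits 1 to 10, and Discontinuation. Each row below also has 15 cells.

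| Row | Marked at | Visit 5 |
|---|---|---|
| Fundus camera/OCT | Screening, V6–V10, Discontinuation | blank |
| Visual acuity | Screening, V6–V10, Discontinuation | blank |
| IOP/slit-lamp | Screening, V2–V10, Discontinuation | marked |
| Fundus examination | Screening, V2–V10, Discontinuation | marked |
| Vital signs | Screening, V1–V5, V8, V10, Discontinuation | marked |

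A shifted column would not leave two complete rows blank at Visit 5 while the rows around them are marked there.

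**3. Whether the next scheduled OCT can serve.**

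- Visit 5: Day 8, window −1 to +3, so Day 7 to Day 11.
- Visit 6: Day 15, window ±3, so Day 12 to Day 18.

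The earliest permitted Visit 6 falls one day after the latest permitted Visit 5. The windows do not overlap, so no OCT within the Visit 6 window is also a Week 1 OCT.

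**4. Whether another provision restores the scan.** Section 8.2.1 names no visit. Section 8 allows off-schedule evaluations for safety or for technical problems with an assessment, which does not describe a routine primary measurement. A discontinuation examination could fall near Day 8, but only for a subject who is leaving the trial.

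**5. Result.** Under literal adherence, 0 of 20 Week 1 OCT scans are planned. With a mark at Visit 5, up to 20 are planned. About 19 remain after the assumed dropout, with power 0.82 at d = 0.7. The sample size itself does not change.

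**The case against.** **The table may have been damaged in conversion.** The copy read here is a text conversion of the PDF, and parts of it are visibly wrong. Blood tests and the chest X-ray carry the footnote for treated-eye-only examinations. The adverse-event row is empty although events are collected throughout. The IOP/slit-lamp cell at Visit 5 carries the treated-eye footnote, whereas Sections 8.2.4 and 8.2.5 confine that restriction to Visits 2, 3 and 4. A full cell count does not prove that every mark survived. This stands as a reason to check the original PDF first. It does not readily explain the consistent pattern in step 2.

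**The intention is clear.** Sections 1.1, 3 and 9.3 all call for a Week 1 OCT, and the subject is in hospital at the trial site on that day. Many sites would scan anyway. This also stands. A reader might infer that the primary analysis will have no data, but the documents support that only for a site that follows one blank cell and disregards the stated endpoint.

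**Two further inferences are tempting but not supported.**

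- *Visual acuity.* Its Visit 5 cell is blank too, but BCVA endpoints exist only at Weeks 4 and 12. No endpoint needs a Week 1 value.
- *Baseline and device.* Screening may precede surgery by up to 7 + 7 = 14 days and may take place at a partner site. Section 8.2.1 says only: "When measurements are performed at the same medical institution, the same device shall be used throughout the clinical trial period, in principle". One might conclude that the pre-post change is biased by a change of device, or that a pre-dose OCT must be mandated. The documents give neither size nor direction for a difference between devices. Section 9.1 already defines baseline as the valid assessment closest to administration, Appendix 4 requires precision management of partner-site devices, and the instrument used is recorded. A compulsory extra scan would be an added procedure and not the correction of an error.

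**Conclusion.** The point holds as an internal contradiction. The binding schedule omits the OCT that the primary endpoint requires, and no other provision puts it back. Under strict adherence the loss is complete (0 of 20). In practice it lies between none and all, depending on how many sites work from the table alone, and the documents give no basis for a narrower estimate. With one subject to spare, even two missing Week 1 scans would take the number of observed values below the planned 19.

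This rests on two assumptions: that the cell is also blank in the original PDF, and that a site reads the schedule as Section 8 tells it to. The first should be verified before anything is changed. The conclusion does not extend to visual acuity, to device bias or to the choice of baseline scan.

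**What to change.** 1. Check the Visit 5 cell of the OCT row in the original PDF of the current protocol version.
2. If it is blank, mark OCT at Visit 5 in Section 1.3 and send sites a short notice, so that no further subject passes Week 1 without the scan.
3. If it was left blank on purpose because tamponade was expected to obscure the macula, reconcile it with the Section 3 rationale, which rests on gas not interfering at Week 1. The two statements cannot both stand.

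The cost is one table cell in an amendment and a site memo. The scan is non-invasive, falls within an existing hospital stay, and is already presupposed by the primary analysis. Sample size and analysis method are unaffected.
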